### Data collection

2.4.

The demographic characteristics questionnaire, Cardiac Self-Efficacy Scale (CSES), MacNew Heart Disease HRQL questionnaire (MNHD-Q), Cardiac Symptom Scale (CSS), and Morisky Medication Adherence Scale will be filled out by the patients. Their caregivers will also fill out the demographic characteristics questionnaire, and Caregiver Burden Scale (CBS). To protect the participants’ confidentiality, the questionnaires will be completed in person at the baseline. All questionnaires, except the demographic questionnaire, will be completed by the participants immediately after the intervention and 2 months after the intervention anonymously and confidentially based on the code assigned to each participant on the WhatsApp.

#### Demographics data questionnaire

2.4.1.

It includes questions about age, gender, income and marital status, height, weight, education level, occupation, smoking, alcohol consumption, diseases’ history, family history of heart surgery, health insurance status, and place of residence. This questionnaire will be assessed through face and content validity before the data collection.

#### Cardiac self-efficacy scale (CSES)

2.4.2.

This questionnaire consists of 13 questions in two subscales of symptom control (8 questions) and performance maintenance (5 questions) on a 5-point Likert scale. Each question is assigned a score between 0 (strongly disagree) and 4 (strongly agree). The range score of self-efficacy is 0–52. The English version of the questionnaire has been validated by Sullivan et al. A high and low score indicates a high and low level self-efficacy, respectively (50, 51). The validity and reliability of the Farsi version of CSES in patients undergoing the CABG surgery has been confirmed via a content validity index (CVI) of 91.33% and Cronbach’s alpha coefficient of 0.97 (48).

#### Macnew heart disease HRQL questionnaire (MNHD-Q)

2.4.3.

It includes 27 questions in three areas of emotional (14 questions), physical (12 questions), and social (13 questions) on a seven-point Likert scale from 1 (the worst conditions related to QoL) to 7 (the best conditions related to QoL) (52). Some questions (*n* = 12) in this questionnaire fall into more than one area. The higher score indicate a higher QoL (53). The validity of MNHD-Q has been approved in Danish, Norwegian and Swedish patients. Also, the reliability assessment of this questionnaire has been supported through Cronbach’s alpha coefficients of 0.94-0.90 (53). The internal consistency of the MNHD-Q in cardiac patients has been reported 0.73 (52). The validity and reliability of Farsi version of the MNHD-Q have been assessed and endorsed on a sample of Iranian patients undergoing the CABG surgery (54).

#### Cardiac symptom scale (CSS)

2.4.4.

It assesses ten cardiac symptoms of angina, shortness of breath, fatigue, depression, trouble sleeping, pain related to incision, swelling of legs, racing heartbeat, anxiety, and poor appetite. These symptoms are measured in three dimensions of the perception of symptoms (yes-no), evaluation of symptoms (frequency and severity), and response to symptoms (interference with physical activity and the enjoyment of life). A score of zero will be given in case of lack of symptoms for three dimensions. A score of 1 is assigned to the perception of symptoms. The scores of frequency and severity, and interference with physical activity and the enjoyment of life range from 1 to 10, and 0 to 10, respectively (43). The validity and reliability of this questionnaire have been confirmed using the CVI score of 0.9–1 and the Cronbach’s alpha coefficient of 85%–98% in patients undergoing the CABG surgery (55).

#### Morisky medication adherence scale

2.4.5.

It includes 8 items, as the first 7 questions have ‘yes’ or ‘no’ answer options. Question 8 has a 5-point Likert scale from ‘always’ to ‘never’ with scores from 0 to 4. The total score of this questionnaire varies from 0 to 8. A score less than 6 indicates low adherence, 6 to <8 is moderate, and 8 shows high adherence. The reliability of the original version of this questionnaire has been confirmed in patients with hypertension with a Cronbach’s alpha coefficient of 0.83 (56). The internal consistency of the Farsi version of this questionnaire has been confirmed with a Cronbach’s alpha coefficient of 0.69 in patients with hypertension (57).

#### Caregiver burden scale (CBS)

2.4.6.

This scale includes 22 questions with five dimensions of general burden (8 questions), isolation (3 questions), frustration (5 questions), emotional conflict (3 questions), and environment (3 questions). Each question is rated on the Likert scale of never, rarely, sometimes, and is scored from 1 to 4. A higher score indicates a greater perceived burden by the caregiver. Internal consistency of this scale has been reported 0.53–0.87 in each domain (58). The validity of the Farsi version of CBS has been approved and its internal consistency through the calculation of the Cronbach’s alpha coefficient has been reported 0.55–0.69. The stability reliability of its domains using the test and retest method has been reported 0.74–0.90 (59).

### Ethical considerations

2.5.

The study protocol has been approved by the ethics committee affiliated with Iran University of Medical Sciences (decree code: IR.IUMS.REC.1400.903). Furthermore, it has been registered on the Iranian Registration Clinical Trials (IRCT) with the code of IRCT20180113038347N2. After obtaining required permissions, the participants will be informed of the study objective and method. All measures will be taken with regard to their anonymity and data confidentiality. They can leave the study at any phase without impacting their care. The participants will be asked to sign the informed consent form before the study.

### Data analysis

2.6.

The two-sided primary statistical hypothesis will be tested as follows: transitional care program from hospital to own home using a digital messaging application has an effect on the health outcomes of patients undergoing CABG surgery and their family caregivers.

Data analysis will be conducted using descriptive and inferential statistics through SPSS statistical software version 25. Demographic and outcome data will be summarized as frequencies (percentages) or means (standard deviation) according to the level of measurement. To test the study hypotheses, the dependent variables will be cardiac self-efficacy, QoL, cardiac symptoms, medication adherence, and caregiver burden across three time points as at the baseline, immediately after the intervention, and two months after the intervention. Inferential statistical tests including repeated ANOVA test will be used. *P*-value will be set at *p* < 0.05. Furthermore, we will consider the intention to treat analysis for non-compliance or incomplete adherence (missing outcomes). Sensitivity analyses will be performed to assess the potential impact of non-response bias on our findings.

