### Participants and sampling

2.2.

After a review of literature (41, 42, 47), eligibility criteria for the recruitment of patients include age over 18 years, CABG surgery for the first time, no other concomitant surgery during the CABG surgery, no history of respiratory diseases, no drug and alcohol addiction, no history of seizure, no psychological and cognitive problems, living with a family caregiver (spouse, children, siblings, other relatives) in own home, being literate as ability to read and write in Farsi, having a smartphone and ability to use WhatsApp, and signing the informed consent form to participate in the study.

In addition, inclusion criteria for family caregivers will be those over 18 years of age, being close family members of the patient, living with the patient, being literate as ability to read and write in Farsi, having a smartphone and ability to use WhatsApp, signing the informed consent form to participate in the study, ability to establish effective communication, experience of patient care undergoing the CABG surgery for the first time, and no history of mental health problems. Moreover, reluctance to participate, re-hospitalization, and patient death during the intervention will be exclusion criteria.

The required sample size has been separately estimated according to the study’s variables in the literature review including the QoL of CABG patients (41); cardiac symptoms (43); cardiac self-efficacy (48); medication adherence (49). The largest sample size (35 patients in each group) belongs to medication adherence using the following formula and its parameters:$$\begin{array}{c} N=\frac{{\left(z_{1-\frac{\alpha }{2}}+z_{1-\beta }\right)}^{2}*{\left(s_{1}+s_{2}\right)}^{2}}{{\left(\mu_{1}-\mu_{2}\right)}^{2}}\\ z_{1-\frac{\alpha }{2}}=1.96\;\;\;z_{1-\beta }=1.29 \end{array}$$μ_1_: The mean of the dependent variable in the intervention group.

S_1_: The standard deviation of the dependent variable in the intervention group.

μ_2_: The mean of the dependent variable in the control group.

S_2_: The standard deviation of the dependent variable in the control group.

α: Type I error.

β: Type II error.

Considering 10% attrition, the sample size will be 40 dyads of patients and caregivers in each group.

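### The primary hypothesis rests on five co-equal outcomes, each at p < 0.05, with no primary outcome or deciding effect named; if any one suffices, the false-positive chance is about 15–23%, not 5%

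*Protocol article*

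**What the plan says.** The Data analysis section (2.6) introduces its hypothesis with "The two-sided primary statistical hypothesis will be tested as follows" and then states that the program "has an effect on the health outcomes of patients undergoing CABG surgery and their family caregivers". To test it, "the dependent variables will be cardiac self-efficacy, QoL, cardiac symptoms, medication adherence, and caregiver burden across three time points". The time points are "at the baseline, immediately after the intervention, and two months after the intervention". On method it says only "Inferential statistical tests including repeated ANOVA test will be used", with a significance level of 0.05.

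The section gives no ranking of the five outcomes, no division of alpha, no testing order and no rule for how many outcomes must be significant. It does not say which ANOVA effect answers the question. The abstract, the aim at the end of the Introduction and the Discussion also list the outcomes without naming a primary one.

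The section on participants and sampling (2.2) sizes the trial by estimating a sample size separately per outcome, each with 1.96 for the significance level, and taking the maximum: "The largest sample size (35 patients in each group) belongs to medication adherence". It names four patient outcomes for this purpose; caregiver burden is not among them.

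**The concern.** A primary hypothesis should be settled by a test whose error rate is known in advance. Here it is worded so broadly that a significant result on any of five outcomes, in two different populations (patients and caregivers), could be presented as confirming it. Each test carries its own 5% risk, so the risk for the overall claim is larger than 5%.

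Taking the largest of several separate sample sizes protects the power of each outcome. It does nothing for the type I error of the joint claim.

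The Conclusion says that a program shown feasible and effective can be incorporated into existing care programs. With no primary outcome or deciding effect fixed, the choice of which result carries that claim can be made after the data are seen.

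**Working it through.** **The plan's own figure.** Section 2.2 gives 35 per group and 10% attrition: 35 / 0.90 = 38.9, so 39, which the plan rounds up to 40 dyads. The 35 itself cannot be reproduced, because the means and standard deviations behind it are not given. The plan states no family-wise error rate, only p < 0.05.

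**Inputs.** Five outcomes, three time points, a repeated-measures ANOVA and a 0.05 level come from section 2.6. The correlations are assumptions, since the document gives none.

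**One test per outcome, independent outcomes.** 1 − 0.95^5 = 1 − 0.774 = 0.226.

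**Correlated outcomes.** Two simulations under no effect were run: multivariate normal test statistics (1,000,000 draws), and the repeated-measures ANOVA itself (35 per arm, three times, five outcomes, 20,000 trials, correlation over time 0.5 or 0.7). The table shows the chance of at least one false positive.

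| Assumed correlation between outcomes | Five tests, normal simulation | Five ANOVA F tests | Group or interaction F may count (ten tests) |
|---|---|---|---|
| 0 | 22.6% | about 23% | about 40% |
| 0.3 | 20.9% | about 21% | about 38% |
| 0.5 | 18.3% | about 19% | about 34% |
| 0.7 | 14.8% | about 15% | about 28% |

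The upper bound for ten tests agrees with the formula for independence: 1 − 0.95^10 = 0.401.

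**Effect of adjustment.** Holm across five outcomes starts at 0.05 / 5 = 0.01. Even plain Bonferroni at that level gives 1 − 0.99^5 = 4.9% for independent outcomes, so control at 5% is restored.

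**Power at the 0.01 level.** The effect size is not given, so it was backed out of n = 35 with 1.96 + 1.29 = 3.25:

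- Standard two-sample formula with 2 × SD²: d = √(3.25² × 2 / 35) = 0.78.
- Formula as printed, (s1 + s2)², with equal SDs: d = √(3.25² × 4 / 35) = 1.10.

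After 10% attrition, 40 × 0.90 = 36 per arm remain. For a two-sample t test, power at alpha 0.05 is 90% for d = 0.78. At alpha 0.01 it is about 74% for d = 0.78 and about 98% for d = 1.10.

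**The case against.** Four points on the other side deserve weight.

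- **No decision rule is stated.** Section 2.6 does not say that one significant outcome is enough, and it also refers to study hypotheses in the plural, which allows an outcome-by-outcome reading. This stands: the error rates above depend on the any-one-suffices assumption. It does not remove the problem, because the text calls one broad statement primary and offers no other rule.
- **Two follow-ups do not mean ten tests.** A reader might infer that each outcome is tested separately at each follow-up, with a false-positive chance of 40%. The document does not support this: it plans a repeated-measures ANOVA across all three time points. Separate tests at two follow-ups would not be independent either, since they use the same outcome in the same people; simulation gives about 24–38% for that design. About 40% is reached only if both the group and the interaction test may count and the outcomes are uncorrelated.
- **Subscales are not planned tests.** The instrument descriptions list subscales, domains and, for the cardiac symptom scale, "These symptoms are measured in three dimensions of the perception of symptoms (yes-no), evaluation of symptoms (frequency and severity), and response to symptoms". A reader might add these to the count. Section 2.6 names five dependent variables and plans no test of a subscale or single symptom, so they do not belong in it.
- **An analysis plan might hold an adjustment.** It might, and detailed multiplicity procedures are often kept there. But the article itself fixes the primary hypothesis, the outcomes and the level, and it is this combination that is badly fixed.

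**Conclusion.** The concern holds. As written, section 2.6 tests one omnibus primary hypothesis through five co-equal outcomes at an unadjusted 0.05, with no primary outcome, no deciding ANOVA effect and no multiplicity control. If one significant ANOVA test suffices, the chance of a false claim is about 15–23% for assumed between-outcome correlations from 0.7 down to 0, which is three to four and a half times the nominal 5%. If either the group or the group-by-time effect may count, it rises to about 28–40% over the same correlations, with 40% as the extreme and not the expected value. These rates rest on assumed correlations and on a decision rule that the wording allows but does not state.

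**What to change.** In section 2.6, name one primary outcome by its total score, with one deciding contrast, and test it at two-sided 5%. Make the other four outcomes secondary. The investigators should make this choice before any outcome data are compared by group. Medication adherence is one candidate because it sets the sample size, but section 2.2 ties the sample size to no visit, so the document does not settle the visit or contrast. The cost is a change of wording; the other four outcomes can then no longer support the primary claim on their own.

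Alternatively, keep five co-primary outcomes, still with one deciding contrast each, apply Holm across them, and restate the power at the smallest adjusted level of 0.01. This costs some power. How much depends on the effect size, which the document does not give: at 36 per arm, power at 0.01 is about 74% if d = 0.78 and about 98% if d = 1.10.

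### Repeated ANOVA with baseline as one of three outcome time points is valid but less efficient than baseline adjustment, and by default it analyses complete cases only

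*Protocol article*

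**What the plan says.** Section 2.6 (Data analysis) makes cardiac self-efficacy, quality of life, cardiac symptoms, medication adherence and caregiver burden the dependent variables "across three time points as at the baseline, immediately after the intervention, and two months after the intervention". Baseline is therefore a level of the outcome. The one test named is in the sentence "Inferential statistical tests including repeated ANOVA test will be used", to be run "through SPSS statistical software version 25" with no procedure specified. The significance level "will be set at *p* < 0.05".

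On incomplete data the same section says "we will consider the intention to treat analysis for non-compliance or incomplete adherence (missing outcomes"), and adds: "Sensitivity analyses will be performed to assess the potential impact of non-response bias on our findings". It mentions neither baseline adjustment, nor a mixed model, nor imputation.

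Two other sections bear on this. Section 2.2 (Participants and sampling) gives 35 patients per group, raised to 40 dyads per group for 10% attrition, and also says that "reluctance to participate, re-hospitalization, and patient death during the intervention will be exclusion criteria". Section 2.4 (Data collection) has patients and caregivers fill in separate scales, with both follow-ups completed over WhatsApp.

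**The concern.** Randomisation makes the expected baseline difference zero, so the baseline score carries no treatment effect. Its value is as a predictor of the later scores. When it enters as a third outcome level, the group-by-time test becomes a two-degree-of-freedom comparison of changes. That is inefficient when baseline and follow-up correlate weakly. A baseline-adjusted model takes from the baseline only as much as the correlation supports.

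Classical repeated-measures ANOVA also needs every level present. A participant who misses one follow-up questionnaire drops out of the analysis of that outcome, baseline and other follow-up included. That is a complete-case analysis. The section's stated intention for missing outcomes is different, and nothing in it connects the two. In an unblinded trial with remote follow-up, non-response may differ between arms.

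At stake are some power, some protection against selective loss, and the form of the result. An F-test for group-by-time is not an estimate of the between-arm difference after the programme or two months later.

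**Working it through.** **The plan's own figures.** 35/0.9 = 38.9, so 39 per group; the stated 40 is consistent. The 35 cannot be rebuilt, because no means or SDs are given. It can be back-solved from z = 1.96 and 1.29:
- variance term read as s1² + s2²: effect = 3.25 × √(2/35) = 0.777 SD
- formula as printed, (s1 + s2)²: effect = 3.25 × 2/√35 = 1.099 SD

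**Assumptions for power** (not in the document): SD 1, n = 35 per arm, the same effect δ at both follow-ups, equal correlation r between all visits, two-sided 5%. Power comes from the noncentral F distribution with noncentrality λ. The first calculation takes δ = 0.6.

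- Group-by-time, F(2, 136): λ = (n/2) × (2/3)δ²/(1 − r) = 17.5 × 0.24/(1 − r) = 4.2/(1 − r)
- Baseline-adjusted, one follow-up, F(1, 67): λ = (n/2) × δ²/(1 − r²) = 6.3/(1 − r²)
- Baseline-adjusted, mean of both follow-ups, F(1, 67): λ = 6.3/[(1 + r)/2 − r²]
- Group main effect over all three visits, F(1, 68): the difference shrinks to (2/3)δ = 0.4, so λ = 17.5 × 0.16/[(1 + 2r)/3] = 2.8/[(1 + 2r)/3]

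| δ = 0.6, n = 35 | r = 0.3 | r = 0.5 | r = 0.7 |
|---|---|---|---|
| Group-by-time | λ 6.0, 57% | λ 8.4, 73% | λ 14.0, 92% |
| Adjusted, one follow-up | λ 6.9, 74% | λ 8.4, 82% | λ 12.4, 93% |
| Adjusted, mean of both | λ 11.25, 91% | λ 12.6, 94% | λ 17.5, 98% |
| Group main effect | λ 5.25, 62% | λ 4.2, 52% | λ 3.5, 45% |

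Over group-by-time, one adjusted follow-up gains about 16, 9 and 1 points. The adjusted mean of both gains about 34, 21 and 6. At r = 0.5 the group-by-time and single-visit tests have the same λ, and the difference is entirely the extra numerator degree of freedom. At r = 0.7 group-by-time has the larger λ, because it uses both follow-ups.

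**At the back-solved effect, δ = 0.777.** Group-by-time: λ = 17.5 × (2/3) × 0.604/(1 − r) = 10.1, 14.1 and 23.5, giving 81%, 92% and 99%. One adjusted follow-up: λ = 17.5 × 0.604/(1 − r²) = 11.6, 14.1 and 20.7, giving 92%, 96% and 99%. At 1.099 SD with 36 per arm, every method has at least 93% for these correlations.

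**Complete cases.** Ten per cent total loss leaves 40 × 0.9 = 36 per arm, above 35. The count falls below 35 only when more than 1 − 35/40 = 12.5% are incomplete. If 10% were missing independently at each follow-up, 40 × 0.9² = 32.4, about 32, would be complete.

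**Selective loss.** Two scenarios were simulated with 40 randomised per arm, 3,000 runs each, and a nominal 20% missing at the last visit depending on the earlier follow-up score.
- δ = 0.5, r = 0.5: the complete-case difference at the last visit averaged 0.48, against 0.51 for the baseline-adjusted likelihood estimate (true value 0.50). Power was 51% for complete-case group-by-time and 62% for the likelihood estimate. Most of that gap is baseline adjustment: with no data missing the corresponding figures are 62% and 72%.
- δ = 0.777, r = 0.7: the complete-case difference was 0.72, against 0.775.

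**The case against.** The strongest reply is that repeated ANOVA on a randomised baseline is valid, that group-by-time is the usual treatment test in this design, and that at the effect implied by the plan's own sample size it reaches the planned 90% at r = 0.5 and 0.7. This stands. The 0.6 SD and the correlations are assumptions, and under the printed formula's 1.099 SD the choice hardly matters. It is also fair to say that the largest gains belong to the mean of both follow-ups, a different contrast from a single visit.

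On missing data, the list of tests is open (the sentence says including), sensitivity analyses for non-response are planned, and an analysis plan that is not shown may name the method. Imputation before repeated ANOVA would keep everyone. This stands as well, and it limits the point to what section 2.6 itself fixes: the outcome levels and the one named test.

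A reader might infer several stronger things that the document does not support:
- That the treatment effect will be diluted to two thirds. This follows only if the group main effect is read as the treatment effect, and the plan does not say so. Nor does it say that the time effect will be read that way.
- That one missed questionnaire removes the whole dyad. The scales are separate, so the default loss is one participant for one outcome. Even that is the method's usual behaviour, not written text.
- That intention to treat is promised and cannot be met. The text says it will be considered, and the named test fails to deliver it only by itself.
- That the sample will fall short. The planned attrition is budgeted; about 32 complete cases needs the heavier pattern shown above.

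**Conclusion.** The point holds as a should-fix. Section 2.6 fixes a valid analysis that uses the baseline inefficiently and, by default, uses complete cases only, beside an intention-to-treat aim to which it is not connected.

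The size depends on quantities that the document does not give. At an assumed 0.6 SD the cost against one adjusted follow-up runs from about 16 points at r = 0.3 to about 1 point at r = 0.7. It is larger against the adjusted mean of both follow-ups. At about 0.78 SD the loss matters mainly at low correlation. The attenuation in the selective-loss simulations is modest and specific to the assumed pattern.

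The exclusion of re-hospitalised, reluctant or deceased participants in section 2.2 pulls against intention to treat more directly than the choice of test does. No change of model resolves that if those participants are left out of the analysis.

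**What to change.** In section 2.6, replace repeated ANOVA by a linear mixed model, fitted with the MIXED procedure in SPSS:
- response: the two follow-up scores
- covariate: the baseline score
- fixed effects: arm, visit and arm-by-visit
- covariance: unstructured
- data: all available data from all randomised participants, for each outcome separately

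Report the adjusted between-arm difference with its 95% confidence interval at each follow-up, or averaged over both, and state beforehand which one decides. Reconcile the phrase all randomised participants with the exclusion wording in section 2.2.

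The cost is wording only: same data, same software. The model spends one degree of freedom on the covariate and assumes that data are missing at random. The planned sensitivity analyses for non-response can probe that assumption.
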